#### Recruitment {15}

Participants in this study will be recruited via flyers on social media (Facebook and Instagram), from references from colleagues (university faculty members, clinicians, and researchers), and via flyers/posters on the University of Buenos Aires.

## Assignment of interventions: allocation

### Sequence generation {16a}

Simple randomization will be used in this study. Participants who met the inclusion criteria will be randomized to either treatment condition (UP) or Wait-List Control, using specific online software (https://www.randomizer.org/). Ratio allocation will be 1:1 (approximately).

### Concealment mechanism {16b}

Treatment group assignment to participants or therapists cannot be concealed due to the nature of psychotherapy interventions. The allocation will be made by a member of the research team who will not be involved in the screening or group treatment.

### Implementation {16c}

A member of the research team who will not be involved in patient recruitment, assessment, or delivering the treatment will perform randomization and allocation.

## Assignment of interventions: blinding

### Who will be blinded {17a}

Due to the nature of this intervention, treatment allocation cannot be blinded to the therapist or participants. Participants will not receive details about the research aims.

### Procedure for unblinding if needed {17b}

This trial is not blinded. Unblinding the allocation will not be necessary at any point.

## Data collection and management

### Plans for assessment and collection of outcomes {18a}

#### Diagnosis (DSM-5 criteria)

A semi-structured online interview will be carried out in order to assess major psychiatric disorders according to the DSM-5 [23]. All the clinicians involved in this work were trained in clinical interviews and psychopathology.

### Demographic and satisfaction/acceptability information

#### Ad-hoc socio-demographic questionnaire

An ad-hoc sociodemographic questionnaire was developed in order to assess age, self-perceived gender, place of residence, and educational level.

#### Ad-hoc acceptability and perceived satisfaction with the treatment questionnaire

An ad-hoc questionnaire was developed with the aim of evaluating the experience with the treatment and the acceptability of the intervention. For this purpose, 9 items were constructed with a Likert-type response format from 1 to 10. This questionnaire was based on the previous study of Osma et al. [14].

### Primary outcome measures

#### ***Beck Depression Inventory-II (BDI II; ***[24]***)***

The BDI II is a questionnaire that was designed to measure the severity of individuals’ depressive symptoms. It contains 21 items that explore the typical symptoms of a major depressive episode. Each item presents 4 alternatives, ranging from 0 (not at all) to 3 (severe, almost intolerable), on a Likert-type scale. It was validated and adapted to the Argentine population, with an appropriate internal consistency (Cronbach’s alpha coefficient of 0.88.)

#### ***Beck Anxiety Inventory (BAI; ***[25]***)***

It is a scale proposed to measure the severity of anxiety symptoms. It is composed of 21 items and each of these items scores from 0 (not at all) to 4 (I could hardly bear it) on a Likert scale. It has been validated in the Argentine population and shows a good internal consistency (Cronbach alpha coefficient of 0.93).

### Secondary outcome measures

#### ***Beck Hopelessness Scale (BHS; ***[26]***)***

This instrument was created to measure pessimism and hopelessness. It consists of 20 items with a true or false response format, with a possible score that ranges from 0 to 20, with higher scores indicating the presence of strong hopelessness. This instrument was previously validated and adapted to Argentina (Cronbach's alpha coefficient of 0.78).

#### ***Difficulties in Emotion Regulation Scale (DERS; ***[27]***)***

This scale measures the degree to which individuals use different emotional regulation strategies. The adapted scale consists of 30 self-administered items with a five-choice Likert-type scale that ranges from 1 (almost never) to 5 (almost always). This scale presents a robust Cronbach's alpha coefficient of 0.94.

#### ***Multicultural Quality of Life Index (MQLI; ***[28]***)***

This scale was created to measure the quality of life in a brief, multicultural, and multidimensional way. In this self-administered 10-item instrument, each item addresses an area of functioning on a Likert-type scale ranging from 1 (poor) to 10 (excellent). All these items are summarized to obtain a Global Quality of Life Index. This instrument was validated and adapted to the Argentine context with a Cronbach’s alpha coefficient of 0.85.

#### ***Positive and Negative Affect Schedule (PANAS; ***[29]***)***

This inventory has been designed to measure affect in a dimensionally way (negative affect and positive affect). It comprises four dimensions: trait positive affect (five items), trait negative affect (five items), state positive affect (five items), and state negative affect (five items). Each item uses a Likert-type scale ranging from 1 (not at all) to 5 (very much or completely). It was validated in Argentina with a good internal consistency (Cronbach’s alpha coefficient of 0.73).

#### Plans to promote participant retention and complete follow-up {18b}

Upon completion of the intervention, participants will be contacted by e-mail and phone calls to encourage them to complete the follow-up.

#### Data management {19}

All data obtained from the screening will be recorded automatically by the secured platform. Patients will accept the informed consent and will be contacted by a researcher of the team for the online interview. The members of the research team in charge of the diagnoses interviews will be trained and will be provided with a semi-structured interview based on DSM-5 in order to unify the criteria. Interview notes will be stored in a secure office at the University of Buenos Aires.

After that, patients’ data will be anonymized by a unique ID code on the dataset and will be stored in a secure server and the computer will have a password to be accessed only by the principal investigators.

#### Confidentiality {27}

Before entering the study, participants will complete the initial screening and the informed consent. Participants’ information will be encoded with a unique ID number in order to maintain confidentiality. The database will be protected on a computer with password security on a secured platform. Only the principal investigator in the research team will have access to the data.

#### Plans for collection, laboratory evaluation, and storage of biological specimens for genetic or molecular analysis in this trial/future use {33}

N/A, no biological samples will be collected.

### Statistical methods

#### Statistical methods for primary and secondary outcomes {20a}

Statistical analysis will be performed with the latest version of SPSS for Windows or R. Sociodemographic variables will be analyzed using descriptive statistics and will be presented in tables. Means and standard deviations will be calculated for numerical variables and frequencies and percentages for categorical variables. The chi-square test and *t-test* will be used in order to examine if group participants differ in their baseline characteristics.

For primary and secondary outcomes, longitudinal changes in each group (T0, T1, T2) and changes between groups will be calculated with a mixed linear model (MANOVA). The effect size for pre and post-treatment and between groups will also be calculated.

A Bonferroni-Holm correction will be conducted as a multivariate correction method to address the issue of multiple comparisons.

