### Trial design {8}

This is the protocol of a parallel-group, controlled, randomized trial, with a pre-post and repeated follow-up measures intergroup design. This trial is framed in the superiority framework.

A two-arm trial is going to be carried out. For this reason, a waiting list has been chosen as a comparator. Participants with low to moderate anxiety/depressive symptoms will be randomly assigned to Group 1: Unified Protocol for Transdiagnostic Treatment of Emotional Disorders (UP) intervention, or Group 2: Wait-List Control group.

The assessment will be conducted at three-time points for Group 1: an initial assessment before being randomized (pretreatment; T0), at the end of the intervention (post-treatment; T1), and 3 months after the completion of the intervention (T2). Group 2 will be assessed on T0 and T1. T2 would not be measured in this group since after T1 they will start treatment.

CONSORT patient’s flowchart is presented in Fig. 1.

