### Outcomes {12}

#### Primary outcomes

In this study, participants are expected to show improvement in anxiety (BAI), and depression (BDI II) at post-treatment (T1) compared to pre-treatment (T0), and this result is expected to remain stable for 3 months (T2). In Wait-List Control, it is expected that there would not be a significant improvement in these variables at T1 compared to T0.

The clinical cut-off point for these scales in the Argentine population is 10 points. A cut-off score ≥ 10 in the BDI and BAI indicates clinical anxiety or depression (mild, moderate, or severe). A score ≤ 10 indicates that symptoms of anxiety or depression are not clinically relevant.

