#### Sample size {14}

The sample size has been estimated based on a meta-analysis of previous studies of the application of the Unified Protocol in emotional disorders compared to a control group [21]. These studies showed a medium effect size (0.45 g* hedges*) on post-treatment measures. A median effect size (0.5) was assumed to detect differences between the intervention and the control group. G*Power software was used to calculate the sample size. For two groups, with a statistical power of 0.80, and an alpha of 0.05, it is estimated that a total of 150 participants will be required (75 for each condition). Given that previous studies have reported a dropout rate between 15 and 20% [22], the total sample required will be 180 participants, 90 for each group.

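### The T1 comparison of BDI-II and BAI is set up as a difference in change from T0, with no stated adjustment for the T0 score; adjustment would be at least as precise, and the power gained depends on a T0–T1 correlation the protocol does not give

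*Protocol article*

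**What the plan says.** All references are to the protocol article; no separate analysis plan was available.

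- **Model and contrast.** Statistical methods {20a} states, for primary and secondary outcomes alike, that "longitudinal changes in each group (T0, T1, T2) and changes between groups will be calculated with a mixed linear model (MANOVA"). No baseline covariate is named, and nothing says that the arms share a T0 mean.
- **Framing of the primary outcomes.** Under Primary outcomes, "participants are expected to show improvement in anxiety (BAI), and depression (BDI II) at post-treatment (T1) compared to pre-treatment (T0"), and the wait-list arm is expected not to improve over the same interval. This too is a comparison of T1 with T0.
- **Timing of baseline.** Trial design {8} places T0 before allocation: "an initial assessment before being randomized (pretreatment; T0").
- **Control-arm visits.** The same section says "Group 2 will be assessed on T0 and T1". T1 is therefore the only follow-up at which the randomised arms can be compared.
- **Other use of baseline.** Statistical methods {20a} adds that "The chi-square test and *t-test* will be used in order to examine if group participants differ in their baseline characteristics".
- **Planning figures.** Sample size {14} cites a Hedges g of 0.45 at post-treatment from a meta-analysis. The planning value is slightly higher: "A median effect size (0.5) was assumed to detect differences between the intervention and the control group". The error rates appear later in the same section: "with a statistical power of 0.80, and an alpha of 0.05". It arrives at 75 per arm, raised to 90 per arm for dropout. No pre-post correlation is stated.

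**The concern.** The superiority question rests on one randomised comparison per primary scale, at T1. Each participant brings a pre-randomisation value of that scale. With T0 treated as a response and its mean left free in each arm, the arm-by-time term over T0 and T1 equals the difference between arms in mean change, whether the model is called MANOVA or mixed.

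A change score gives T0 a fixed weight of one. Regression on T0 lets the data choose the weight, which with equal SDs is rho. For any rho below 1 the fixed weight is too large, and the estimate carries avoidable noise. At stake are wider confidence intervals and lower power than the same data could give. This matters most if the true effect is nearer the cited 0.45 than the assumed 0.5, or if the Holm correction makes the first test of the two primary scales use alpha 0.025.

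**Working it through.** **The plan's own figure.** A two-sided two-sample t test with d = 0.5, alpha 0.05 and power 0.80 needs 64 per arm (128 in total). With d = 0.45 it needs 79 per arm (158). The stated 75 per arm (150) follows from neither. Because it is the evaluable size the protocol fixes, it is used below as given.

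**Inputs from the protocol.** n = 75 per arm evaluable and 90 per arm randomised; d = 0.5 (assumed effect) and g = 0.45 (cited meta-analysis); alpha 0.05.

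**Assumptions, not in the protocol.** Two-sided testing; effect in units of the T1 SD; rho varied from 0.3 to 0.8; T0 and T1 SDs equal at first, then varied.

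**Variances, in units of the squared T1 SD, equal SDs.**
- Difference in change: v = 1 + 1 − 2·rho = 2(1 − rho).
- T1 adjusted for T0: v = 1 − rho².
- Ratio: 2(1 − rho)/[(1 − rho)(1 + rho)] = 2/(1 + rho), above 1 for every rho below 1.

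At rho = 0.5 these are 1.00 and 0.75. The change score is then no more precise than ignoring T0 altogether (v = 1), while adjustment cuts the variance by 25%. Below rho = 0.5 the change score is worse than ignoring T0.

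**Power.** Noncentral t with noncentrality (d/√v)·√(n/2), on 2n − 2 df for change and 2n − 3 df for the adjusted analysis. Example at d = 0.5, rho = 0.5, n = 75: √37.5 = 6.124, so the noncentrality is 0.5 × 6.124 = 3.06 for change and 3.06/√0.75 = 3.54 adjusted. Power is 86.0% and 94.0%.

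75 per arm, alpha 0.05, equal SDs (change → adjusted):

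| rho | d = 0.5 | gain | g = 0.45 | gain |
|---|---|---|---|---|
| 0.3 | 72.9% → 89.0% | 16 | 63.8% → 81.9% | 18 |
| 0.4 | 79.3% → 91.3% | 12 | 70.5% → 84.8% | 14 |
| 0.5 | 86.0% → 94.0% | 8 | 78.2% → 88.5% | 10 |
| 0.6 | 92.5% → 96.7% | 4 | 86.5% → 92.8% | 6 |
| 0.7 | 97.5% → 98.9% | 1 | 94.2% → 96.9% | 3 |
| 0.8 | 99.8% → 99.9% | 0.1 | 99.1% → 99.5% | 0.4 |

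**Unequal SDs.** If the T0 SD is k times the T1 SD, the change variance is 1 + k² − 2·k·rho and the adjusted variance is still 1 − rho². At rho = 0.5, d = 0.5, 75 per arm (adjusted power 94.0% throughout):

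| k | change variance | change power | gain |
|---|---|---|---|
| 0.7 | 0.79 | 92.8% | 1.2 |
| 0.8 | 0.84 | 91.3% | 2.7 |
| 0.9 | 0.91 | 89.0% | 4.9 |
| 1.1 | 1.11 | 82.3% | 11.7 |

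**All 90 per arm analysed, rho 0.5, alpha 0.05, equal SDs.** d = 0.5: 91.6% → 97.1%. g = 0.45: 85.1% → 93.4%. The gain is about 5 to 8 points.

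**First Holm step, if applied to the two primary scales (alpha 0.025), 75 per arm, rho 0.5, equal SDs.** d = 0.5: 78.7% → 89.7%. g = 0.45: 68.8% → 81.9%.

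**The case against.** **The model might already be efficient.** A mixed model that constrains the arms to one T0 mean also carries T0 as a repeated response, and it is about as precise as covariate adjustment. The article is condensed and does not rule this out, so it would be too strong to say the trial has decided against adjustment. What remains is that the article does name a model and a contrast, and both the MANOVA label and the comparison of changes point to the unconstrained form. If the constrained form is meant, one clause settles it.

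**The size is not fixed by the documents.** A reader might infer a definite loss of 8 to 10 points. The documents do not support that, since it needs rho near 0.5 and equal SDs. Trial design {8} describes participants with low to moderate symptoms, which could narrow the T0 spread and shrink the gain. Missing values are to be imputed, so up to 90 per arm may enter the analysis; imputation does not restore all the lost information, so the 90-per-arm figures are the favourable end.

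**The power target need not be missed.** At d = 0.5, rho = 0.5 and alpha 0.05 the change contrast still has 86.0%. This stands. Power falls below 80% at lower rho, at g = 0.45 with rho 0.5, or at the first Holm step with rho 0.5.

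**Bias.** Simple randomisation does not limit chance imbalance in T0, and a reader might infer that the change score biases the result towards the arm that starts worse. It does not: across randomisations the estimate is unbiased. Given a particular imbalance it over-corrects, but modestly. With 90 per arm the standard error of the T0 difference is √(2/90) = 0.149 SD, and at rho = 0.5 the over-correction for an imbalance of that size is (1 − 0.5) × 0.149, about 0.07 SD. This is the same imprecision already counted in the variance.

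**Baseline significance tests.** They do not enter the primary estimate. Dropping them is a reporting preference and adds nothing to this point.

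**Conclusion.** The point holds as one of efficiency, not validity. As written, the T0–T1 contrast is a difference in change scores, and adjusting T1 for T0 would be at least as precise apart from one degree of freedom. At 75 per arm, two-sided alpha 0.05 and equal SDs, the gain at d = 0.5 to g = 0.45 is about 8 to 10 power points if rho is 0.5, 16 to 18 if 0.3, 1 to 3 if 0.7, and under 1 if 0.8. At rho 0.5 and d = 0.5 it shrinks to 1 to 5 points if the T0 SD is 0.7 to 0.9 of the T1 SD, and rises to about 12 if it is 1.1 times the T1 SD. That the analysis uses separate T0 means per arm is a reading of the text, the more natural one but not stated outright.

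**What to change.** In Statistical methods {20a}, state the primary analysis for each of BDI-II and BAI as the between-arm difference at T1 from a linear model with arm and the same scale's T0 score. Alternatively, specify a mixed model in which the two arms are constrained to a common T0 mean. Use the same form for each secondary scale with its own T0 score. If a common T0 mean was always intended, say so.

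The cost is a change of wording and one degree of freedom per model. The T0 scores are already collected and both forms can be fitted with standard software. No extra participants, visits or measurements are needed.

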### Wait-List Control

Participants in the waiting list control will receive the same intervention as described above after the end of the group intervention. Participants on the waiting list will complete the same assessments as the intervention group (T0, T1), except the last one (T2).

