#### Methods in analysis to handle protocol non-adherence and any statistical methods to handle missing data {20c}

To address protocol non-adherence, participant education will emphasize the importance of adhering to the protocol, while clear instructions and materials will be provided. Investigators and research staff will receive training and ongoing support. For this, monitoring and supervision procedures will be implemented to detect and correct deviations. Standardization of intervention and data collection procedures across sites will be ensured. Moreover, motivational strategies will be carried out to encourage adherence while barriers to adherence will be identified and addressed.

Missing data will be imputed using the random forest method.

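### The analysis sentence covers T0, T1 and T2 in both arms under two model names, but the wait-list has no T2, and the imputation rule does not exempt that absent visit

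*Protocol article*

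**What the plan says.** Under Statistical methods for primary and secondary outcomes {20a}, one sentence sets the analysis of every outcome: "longitudinal changes in each group (T0, T1, T2) and changes between groups will be calculated with a mixed linear model (MANOVA").

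The visit schedule is different. Trial design {8} says "Group 2 will be assessed on T0 and T1", and gives the reason: "T2 would not be measured in this group since after T1 they will start treatment". The Wait-List Control section repeats it: "Participants on the waiting list will complete the same assessments as the intervention group (T0, T1), except the last one (T2").

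The only rule for missing values, in section {20c}, is "Missing data will be imputed using the random forest method".

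Under Primary outcomes, the expectation for treated participants is improvement from T0 to T1, and "this result is expected to remain stable for 3 months (T2"). For the wait-list, "it is expected that there would not be a significant improvement in these variables at T1 compared to T0". The secondary outcomes follow the same pattern.

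**The concern.** Each group includes the wait-list, so the analysis sentence asks for a three-visit trajectory in an arm that has two visits. Two features of the text make this more than a slip in listing visits.

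First, a linear mixed model and a MANOVA are different procedures, and this data structure is where they part. A likelihood-based mixed model uses whatever visits each person has. A classical repeated-measures MANOVA needs a complete vector from each person.

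Second, the imputation rule does not separate a visit that was missed from a visit that was never scheduled. An analyst who applies the sections as written could produce wait-list T2 values with no wait-list observation behind them.

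At stake is any between-arm or group-by-time result that includes T2. It would come from the imputation model, or from an analysis without controls. If the choice of route is left open, it may be made after the data are seen.

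**Working it through.** The plan gives no figure on this point to reproduce, so the check is structural, with an illustration under stated assumptions.

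**Inputs from the protocol.** 90 per arm (Sample size {14}); three visits in the UP arm and two in the wait-list (Trial design {8}); assumed T1 effect 0.5 (Sample size {14}). Dropout is set to zero for the count.

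**1. What can be observed.**
- UP: 90 × 3 = 270 values. Wait-list: 90 × 2 = 180 values. Total 450.
- Both arms at three visits would give 180 × 3 = 540. The gap is 540 − 450 = 90, which is every wait-list T2 value.

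**2. Complete cases over T0, T1 and T2.** UP 90 of 90; wait-list 0 of 90. A MANOVA on these cases has no comparator.

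**3. Estimability.** A full group-by-time model has 2 × 3 = 6 mean parameters. Only 5 arm-by-visit cells hold data, and the design matrix has 6 columns and rank 5. The group-by-T2 term is not estimable.

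**4. What remains estimable.** A mixed model fitted to the 5 observed cells in simulated data (90 per arm) converges and keeps both arms. It gives the between-arm T0-T1 comparison and the T1-T2 change within UP.

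**5. What imputation would put in the empty cell.** Assumptions not in the documents: SD 1, equal correlation ρ between visits, UP means 0, −0.5, −0.5, wait-list means 0 and 0 at T0 and T1.
- Regressing T2 on T0 and T1 in the UP arm gives each slope as b = ρ/(1 + ρ).
- Applied to the wait-list, the imputed T2 mean is −0.5 + b × 0.5.
- With ρ = 0.5: b = 0.333, so the imputed mean is −0.5 + 0.167 = −0.333.
- The true wait-list T2 mean does not appear in the formula.

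Simulation agrees:

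| True wait-list T2 mean | Imputed, regression | Imputed, random forest |
|---|---|---|
| 0 | −0.325 | −0.340 |
| −0.5 | −0.325 | −0.334 |
| +0.3 | −0.331 | −0.351 |

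The imputed value stays near −0.33 whatever the truth, because it carries only the UP arm's T2 relation.

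**6. Size of the artefact, if someone compared arms at T2.** The UP mean minus the imputed wait-list mean is −0.5 − (−0.5 + 0.5b) = −0.5b. For ρ = 0.4, 0.5, 0.6 and 0.7 this is −0.14, −0.17, −0.19 and −0.21 SD. It depends on the assumed ρ and on a comparison that the protocol does not describe.

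**The case against.** The best defence is that the list of visits only names the trial's time points, and that the authors know the wait-list has no T2 because they say so twice and give the reason. The outcome sections support this: the wait-list expectation is stated for T1 against T0 only, and no between-arm contrast at T2 is described. The main term in the analysis sentence is the mixed model, with MANOVA only in brackets, and a likelihood-based mixed model handles the design without harm. Complete-case analysis is not mentioned anywhere. Most of this stands as a limit on the consequences. It does not remove the conflict, since the sentence says each group, does not say which method governs, and the imputation rule has no exception.

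Three stronger readings are tempting and are not supported.

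- *Control T2 must be invented or the control arm lost.* These are two literal routes, not the only ones. The mixed model avoids both and leaves the randomised T0-T1 comparison intact.
- *The stability expectation cannot be tested.* It concerns treated participants, and the UP arm has T1 and T2, so the within-arm change can be estimated. The protocol does not say that stability will be concluded from a non-significant test. Any maintenance margin may sit in a fuller document that is not shown.
- *The plan carries a false-positive rate of about 25% at T2.* That figure arises with 75 per arm, ρ = 0.6, single deterministic regression imputation and a T2 t-test. Added residual noise brings it to about 20%, and 20-fold multiple imputation with Rubin's rules to about 4%. The protocol names a random forest, does not say single or multiple, and plans no such test.

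**Conclusion.** The point holds as a contradiction in the text with a structural consequence. The analysis sentence conflicts with the trial design and wait-list sections on whether the wait-list has T2. It names two methods that treat these data differently, and the missing-data rule does not exclude a visit that is absent by design. Taken literally, either 90 of 90 wait-list T2 values are filled from UP-arm data alone, or a complete-case MANOVA retains 0 of 90 controls. No information on the wait-list at T2 exists, and group-by-T2 is not estimable under any method.

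The counts rest on 90 per arm without dropout; the rank argument does not depend on sample size. The illustration of imputed means rests on the assumed SD, correlation and UP means. The randomised comparison at T1, which answers the efficacy question, is recoverable in full. The T1-T2 change in the UP arm is estimable, but it is uncontrolled and cannot be attributed to the intervention by comparison with the wait-list.

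**What to change.** - **Section {20a}:** delete the bracketed MANOVA and specify a likelihood-based linear mixed model. State that the between-arm comparison is at T1, using T0 and T1 data from both arms.
- **Section {20c}:** state that wait-list T2 is absent by design and is not imputed.
- **T2:** analyse it in the UP arm only. Report the T1-T2 change with a 95% CI, label it uncontrolled, and state that stability will not be inferred from a non-significant change.

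This changes analysis wording only, with no effect on design, visits or sample size. The price is a more modest statement about T2. The change should be made before the outcome data are analysed, so that the choice between the two methods is not made with results in view.

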#### Intervention description {11a}

## Unified Protocol

The UP focuses on different strategies of emotion regulation to address neuroticism, a common factor in all emotional disorders (ED). This intervention intends to address dysfunctional emotional regulation strategies in participants and encourages the use of more adaptive strategies to promote tolerance to intense negative emotions. Participants will receive online, synchronous group therapy based on the UP model for 10 subsequent weeks, with a duration of 90 min for each meeting. After every session, they will receive the chapter of the UP’s Spanish patient’s workbook [6] with the notions addressed in the session and the indications to practice during the week.

Contents of each session:Session 1:

Coordinators’ and participants’ introductions. Session framework. Introduction to the approach and ED. Conceptualization of ED and identification of their own intense emotions, aversive reactions, and avoidance efforts.Session 2:

Module 1: Motivation for change and commitment to treatment. Describing issues, goals, and steps to accomplish them. Introduction to change motivation. Decision balance exercise.Session 3:

Module 2: Understanding emotions. Introduction to the topic of this session (psychoeducation of emotions). Presentation of the three-component model and introduction to the concept of Emotion-Driven Behaviors (EDBs), as well as the antecedents and consequences of emotional experiences.Session 4:

Module 3: Emotional awareness training. Introduction to mindfulness. Non-judgment emotional awareness exercises will be carried out during the session, and participants will receive afterwards by email with the taped audio so as to do it during the week. Introduction to emotional induction and practicing mindfulness when facing stimuli that trigger emotions (videos/audio). Introduction to anchoring in the present.Session 5:

Module 5: Cognitive flexibility. Introduction to cognitive flexibility. Ambiguous image exercise. Introduction to mind traps and cognitive re-evaluation exercise during the session.Session 6:

Module 5: Emotional avoidance and EDBs. Introduction to emotional behaviors. Introduction to EDBs and avoidance types. A cognitive suppression exercise will be carried out during the session. Working with alternative actions.Session 7:

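### UP is given in therapy groups and the wait-list is not, but neither the model nor the sample size allows for clustering in one arm; how much error and power suffer depends on a group size and ICC that the protocol does not state

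*Protocol article*

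**What the plan says.** All places are in the protocol article.

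- **Delivery.** Under the heading Unified Protocol: "Participants will receive online, synchronous group therapy based on the UP model for 10 subsequent weeks". Members of a group share sessions, exercises and therapists.
- **Comparator.** Trial design {8} and Wait-List Control: these participants are assessed at T0 and T1 and start treatment only after T1.
- **Allocation.** Sequence generation {16a}: individuals are randomised by simple randomisation, approximately 1:1.
- **Sample size {14}.** The meta-analysis cited gave a Hedges g of 0.45, and then "A median effect size (0.5) was assumed to detect differences between the intervention and the control group". The calculation is described as "For two groups, with a statistical power of 0.80, and an alpha of 0.05", and "it is estimated that a total of 150 participants will be required (75 for each condition"). This is raised to 180 for dropout. No therapy-group size, number of groups, ICC or design effect appears.
- **Analysis.** Statistical methods {20a}: longitudinal changes over T0, T1 and T2 within each group and "changes between groups will be calculated with a mixed linear model (MANOVA"). In that sentence the groups are the trial arms. No therapy-group or therapist term is named there or anywhere else.

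**The concern.** This is a partially nested design: randomisation is individual, but after it one arm is gathered into therapy groups and the other is not. Group dynamics, shared therapists and shared sessions can make members of a UP group resemble each other at T1. A MANOVA treats every participant as independent. So does a mixed model whose only random structure is repeated measures within a person. If members of a group are positively correlated, the UP-arm mean varies more than such a model believes.

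The claim at stake is superiority on two primary outcomes, BDI-II and BAI. The planned Bonferroni-Holm correction does not protect it, because Holm controls the familywise error only if each p-value entering it is valid. The power figure has the same gap, since it comes from a formula for independent observations.

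**Working it through.** **Inputs from the protocol.** Alpha 0.05 (taken as two-sided; sidedness is not stated), power 0.80, d = 0.5 assumed, g = 0.45 cited, 75 evaluable per arm.

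**Inputs assumed.** Evaluable members per therapy group m = 8 to 12; ICC = 0.02 to 0.10. Neither is in the protocol.

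**1. The plan's own figure.** n per arm = 2 × ((1.960 + 0.842)/d)².
- d = 0.5: 62.8, so 63 per arm (126 in total), or 64 per arm (128) by the t-test.
- d = 0.45: 77.5, so 78 per arm (156), or 79 (158) by the t-test.

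The stated 75 per arm (150) matches neither. With 75 per arm and independent observations, noncentral-t power is 0.86 at d = 0.5 and 0.78 at d = 0.45. So at d = 0.5 the plan holds some slack above 0.80, and at the cited g it holds none.

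**2. Variance with clustering in the UP arm only.**
- UP-arm design effect: DE = 1 + (m − 1) × ICC.
- Var(difference) = SD² × (DE/75 + 1/75).
- Inflation over the independence value: F = (1 + DE)/2.

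**3. Type I error of the test that ignores clustering.** 2 × (1 − Φ(1.96/√F)).

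| m, ICC | DE | F | √F | 1.96/√F | Type I error |
|---|---|---|---|---|---|
| 8, 0.02 | 1.14 | 1.07 | 1.034 | 1.895 | 5.8% |
| 10, 0.05 | 1.45 | 1.225 | 1.107 | 1.771 | 7.7% |
| 12, 0.10 | 2.10 | 1.55 | 1.245 | 1.574 | 11.5% |

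A simulation of a naive t-test on this design, 20,000 runs per row, gave 5.8%, 7.5% and 11.1%.

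**4. Power of a test with the correct standard error, 75 per arm.** Noncentrality is d/√((1 + DE)/75). Two sets of degrees of freedom (df) are used: 148, as if participants were the units, and Satterthwaite, (1 + DE)²/(DE²/(k − 1) + 1/74), where k = 75/m is the number of therapy groups.

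| m, ICC | k | Satterthwaite df | d = 0.5: df 148 / Satterthwaite | d = 0.45: df 148 / Satterthwaite |
|---|---|---|---|---|
| 8, 0.02 | 9.4 | 27 | 0.84 / 0.81 | 0.75 / 0.73 |
| 10, 0.05 | 7.5 | 18 | 0.78 / 0.74 | 0.70 / 0.65 |
| 12, 0.10 | 6.25 | 11 | 0.69 / 0.61 | 0.59 / 0.53 |

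**5. Where power crosses 0.80 at d = 0.5.** By the normal approximation, 75 = (1 + DE) × (2.802/0.5)² gives DE = 1.39. That corresponds to an ICC of about 0.056 at m = 8, 0.043 at m = 10 and 0.035 at m = 12. With Satterthwaite df the crossing comes earlier: at ICC 0.02 power is 0.81 for m = 8, 0.80 for m = 10 and 0.78 for m = 12.

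These are calculations for a comparison of T1 means. The planned model also uses T0, and the baseline correlation, which the protocol does not give, would change both the power and the error figures.

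**The case against.** The strongest reply has three parts.

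**The power statement.** A reader might infer that the stated 0.80 is simply overstated. The protocol does not support that. At its own planning effect the 150 evaluable participants exceed the 126 to 128 required, and the slack absorbs a UP-arm design effect of up to about 1.39. The range at d = 0.5 lies on both sides of 0.80. The shortfall at g = 0.45 exists before any clustering and is a separate matter of effect-size choice. This part of the reply stands.

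**The inputs.** Group size and ICC are assumed throughout. With an ICC of zero the standard errors are right, and at the low end the type I error is 5.8%, a small distortion. A reader might take 5.8% to 11.5% as the trial's actual error rate; it is only what follows from those assumptions. This also stands.

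**The model.** A mixed linear model can carry a therapy-group effect, and a condensed article may leave random effects to an analysis plan that is not shown. This stands only in part. The article equates the model with MANOVA, which has no such term, and describes it by time and arm alone. The sample size is likewise a stated two-group calculation with nothing added for clustering. What is written is a choice that leaves the nesting out, not a detail left open.

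**Conclusion.** The omission is certain: nothing in the protocol allows for therapy-group clustering in the UP arm. The consequence is conditional. Followed as written, the analysis gives standard errors that are too small whenever the ICC is positive, with a type I error of about 5.8% to 11.5% under the assumed ranges. Power at d = 0.5 lies between 0.84 and 0.69 with participant-level degrees of freedom, and between 0.81 and 0.61 for the analysis recommended here. Whether it falls below 0.80 cannot be settled from the document. The validity of the primary p-values is the stronger reason to act; the power figure is secondary.

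**What to change.** 1. Record the therapy-group ID of every UP participant.
2. In Statistical methods {20a}, replace the MANOVA label with a linear mixed model that has a therapy-group random effect in the UP arm only, each wait-list participant being a cluster of one. Use Satterthwaite or Kenward-Roger degrees of freedom, and report the estimated ICC.
3. In Sample size {14}, state the planned therapy-group size and a range of ICCs, and give the power of 75 per arm under them.

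The trial need not be enlarged for this. At d = 0.5 the evaluable total for 0.80 power runs, by the normal approximation, from 136 (m = 8, ICC 0.02) to 196 (m = 12, ICC 0.10), and the protocol offers no basis for choosing within that range. The validity of the test is repaired by the model, not by more participants.

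The cost is one identifier and one model term, slightly wider intervals and a less favourable power figure. With about 6 to 9 groups the variance component will be imprecise and may be estimated at zero, so the plan should say in advance what is reported in that case.
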